##### Mental health

Kessler Psychological Distress Scale [Kessler-10; (43)] a 10-item scale of non-specific psychological distress. Low scores (10–15) indicate little or no psychological distress and higher scores indicate increasing levels of distress (moderate, 16–21; high, 22–29; and very high, 30–50). It has shown consistent psychometric properties across major sociodemographic subsamples (54).

##### Substance use

The Alcohol Use Disorders Identification Test—Brief [AUDIT-C; (40)] a three item screening tool used to identify hazardous alcohol use or active alcohol use disorders. It is scored on a scale of 0–12 with a cut off of 3 (women) or 4 (men). For men, it has been shown to have a sensitivity of 0.90 and specificity of 0.45; for women the sensitivity is 0.80, and specificity is 0.87.

The Cannabis Use Disorders Identification Test—Revised [CUDIT-R; (42)] is a briefer (8-item) and more refined version of the CUDIT (55), a simple modification of the AUDIT. Items cover the domains of consumption, cannabis problems, dependence, and psychological features. The CUDIT-R was found to comprise a single factor, with high test-retest reliability (*r* = 0.871), high internal consistency (α = 0.914), and discriminant validity (area under the curve = 0.960). Only question 1, “How often do you use cannabis? (over the last 2 months)” is included in the present study (never, monthly or less, 2 to 4 times a month, 2 to 3 times a week, 4 or more times a week). In addition, participants who use cannabis are asked “Do you ever mix tobacco with your cannabis?” with response options of “Yes, always or nearly always,” “Yes, sometimes” or “No, never or very rarely.”

##### Quality of life

The Assessment of Quality of Life 8 Dimension [AQoL-8D; (41)] instrument is comprised of 35 items from which eight dimensions (independent living, pain, senses, mental health, happiness, coping, relationships, and self-worth) and two “super-dimensions” (physical and psychosocial) are derived. It has demonstrated strong content validity and has been found to perform relatively well in populations with SMI (56). The 35 items may be reduced to a single utility score. Use of the instrument enables calculation of quality adjusted life years (QALYs) experienced across the two study arms, which will be reported in the cost-effectiveness analysis.

##### Covariate or process measures

Demographic variables (e.g., gender and age).

History of tobacco smoking and quitting.

Types of tobacco used.

Social influences on smoking, e.g., lives with other smokers.

Smoking Use Motives: As part of this trial self-reported reasons for smoking are assessed using a modified version of the Drinking Motives Questionnaire (57), with additional items developed by Spencer et al. (58) to explore the use of substances to alleviate psychotic symptoms (positive and negative).

At baseline, participants will be asked whether they have a preference for in person or telephone counseling. They will also be asked to rate the likely helpfulness of NRT to long term quitting (not at all, some, moderately, extremely) and likelihood of use in the longer term (not at all, some, moderately, extremely).

Motivation to quit: assessed by a single question adapted from Crittenden et al. (59), “How much do you want to quit smoking?” (not at all, a little, some, very much). At follow-up assessments, “Are you trying to quit smoking altogether or are you planning to keep smoking at this level?”

Confidence to quit (at baseline) is measured by the following question: “How confident are you that you can stop smoking for good in the next 2 months if you wanted to?” (not at all, somewhat, moderately, very, extremely).

Self-efficacy in quitting is measured by the following question adapted from Perkins et al. (60): “How confident are you that you will not smoke at all tomorrow?” (not at all, somewhat, moderately, very, extremely). For those who quit at follow-up, “How confident are you that you will be able to stay quit long-term and become a permanent ex-smoker?” (not at all, somewhat, moderately, very, extremely).

Medications: Changes in use of prescribed psychotropicmedication.

Medication side effects: At baseline, participants will be asked to rate 10 symptoms during the past week (e.g., dry mouth, increased thirst) on an ordinal scale from 0 (not present) to 3 (severe). This measure is informed by the most common adverse side effects of psychiatric medications as identified in the Side Effect Survey, which has demonstrated validity and reliability (61).

Treatment received (use of NRT and Quitline—number and length of calls).

Objective data on service use (number and length of calls) will be extracted from the Quitline database for all participants (as some control participants may have self-referred).

Therapeutic alliance with Quitline counselor: the three-item Working Alliance Inventory for Tobacco (45), measuring goal, task, and bond on a five item Likert Scale (seldom, sometimes, fairly often, very often, always) will be administered at the 2-month follow-up. The three-item measure has been found to have acceptable-good internal consistency and construct validity.

Self-reported service use and satisfaction: participants' use and assessment of level of support they have received for quitting from their mental health service, doctors, and other health professionals.

Linked data on service and prescription medication use from the Australian Government subsidized Medicare and Pharmaceutical Benefits Schemes.

##### Safety data

Adverse events will be collected at all follow-up time points, with prompting via questions asking how the participant has been feeling in general and if they have any health concerns.

### Sample Size Determination

Based on our previous study (23) which achieved a 15% prolonged abstinence rate in depressed smokers, and knowing rates are considerably less among those with more severe mental illnesses (62) we anticipate that for the primary outcome of prolonged abstinence at 8 months, prolonged abstinence will occur in 1% of the control arm vs. 8% in the intervention arm. To detect this effect with 80% power at *p* = 0.05, we require 134 per arm. We expect ~30% attrition, inflating the sample size to 191/arm or 382 overall. Thus, we will recruit 382 smokers over 36 months and follow up at 2-, 5-, and 8-months post-baseline, completing the study over a 4.5-year period.

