### Randomization

Following completion of the baseline assessment, a brief intervention will be delivered by a peer worker—prior to randomization—to ensure all participants receive the recommended minimum standard care, in a manner that is unbiased by the outcome of randomization. Following this, the computer program used to complete the baseline will randomize to condition using 1:1 randomization. Participants will be randomly allocated to either no further intervention, or to be contacted by Quitline who will offer a targeted callback counseling intervention with NRT provided, over an 8-week period. As stated above, cluster randomization will be used in situations where risk of contamination is higher, such as residential services, stratified by short- or long-term residence, with 1:1 allocation. Individual randomization will be used in services where contamination of risk is lower, via permutated block sizes of 4 and 6 to avoid incomplete blocks, stratified for site. Participants will be allocated a unique computer-generated study number. Randomization will be independently managed by the trial epidemiologist (JA) and uploaded to a web-based data capture tool (Research Electronic Data Capture; REDCap) that will also have case report forms (eCRF) created for the project using REDCap.

Following randomization, those in the intervention group will be told of the additional supports they will be getting (see above). Controls will be simply told the session is over and reminded of when the first follow-up survey might be expected.

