### Statistical Methods

#### Primary and Secondary Outcomes

Independent and blinded statisticians from the CReDITSS Unit at the Hunter Medical Research Institute, Australia, supervised by [name], will conduct analyses of the primary and secondary outcomes.

Analyses will be carried out using a cluster randomized trial framework where the individuals (*n* = 150) are treated as clusters that contribute only one person, the short-term residential programs are clusters that contribute an average of 15 people each (10 programs × 15 people/program = 150 total) and the long-term programs are clusters that contribute 10 people each (6 programs × 10 people/program = 60). We will use a generalized linear mixed model (linear regression for continuous outcomes and logistic regression for dichotomous outcomes) to handle the clustering and the repeated measures at baseline, 2-, 5-, and 8-months; individuals will be modeled as random effects, cluster as a random effect, and group assignment as a fixed effect. Mixed models allow for missing data for the primary intention to treat analysis, but a sensitivity analysis using a worst case scenario (baseline value for continuous outcomes or relapse for dichotomous outcomes in case of missing value) will also be carried out.

Intervention participants who do not complete the intervention, and participants who miss an assessment follow-up time point, will be kept in the study and contacted for later assessments (unless they choose to withdraw from the follow-up assessments).

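### At the plan's own 1% control rate there is a 26% chance of no control abstainers, where ordinary logistic (mixed) regression gives no finite odds ratio; with a Wald test, power would be about 55%, not 80%

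*Protocol article*

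**What the plan says.** Under Sample Size Determination, the article anticipates that "prolonged abstinence will occur in 1% of the control arm vs. 8% in the intervention arm" and concludes: "To detect this effect with 80% power at *p* = 0.05, we require 134 per arm". It then allows for dropout: "We expect ~30% attrition, inflating the sample size to 191/arm or 382 overall". Allocation is 1:1 (Randomization).

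Under Statistical Methods, Primary and Secondary Outcomes, the model is a generalized linear mixed model, with "linear regression for continuous outcomes and logistic regression for dichotomous outcomes". Its structure is that "individuals will be modeled as random effects, cluster as a random effect, and group assignment as a fixed effect". The primary analysis relies on the mixed model to deal with missing values. A sensitivity analysis counts missing binary outcomes as relapse.

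The article does not say how the group effect will be tested (Wald, score, likelihood ratio or other), or what estimate and interval will be reported if an arm has no events.

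**The concern.** The sample size comes from comparing two proportions, where a control count of zero causes no difficulty. The analysis is on the log-odds scale, where it does. If no control participant is abstinent, the likelihood keeps rising as the control log odds fall without limit (separation). The group odds ratio then has no finite maximum-likelihood value, and a random intercept for cluster does not cure this. The Wald standard error explodes and the Wald p-value tends to 1, so the data most favourable to the intervention give the least usable output.

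Two things are at stake: whether the primary analysis can report an effect estimate at all, and whether the 80% power holds for the test actually used. A remedy chosen after seeing an empty control arm would be data-dependent.

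**Working it through.** **Inputs.** From Sample Size Determination: control rate 0.01, intervention rate 0.08, alpha 0.05, power 80%, 134 per arm, about 30% attrition, 191 per arm. From Randomization: 1:1. From Statistical Methods: logistic mixed model. Assumptions: alpha is two-sided (not stated), and the test statistic is varied because none is named.

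**1. The plan's figure.** Two-proportion normal formula with unpooled variance: n = (1.960 + 0.842)² × (0.01×0.99 + 0.08×0.92) / 0.07² = 133.75, so 134 per arm. Attrition: 134/0.7 = 191.4, stated as 191. Both figures reproduce.

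**2. Expected events.** Control 134 × 0.01 = 1.34; intervention 134 × 0.08 = 10.7.

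**3. Chance of an empty control arm.**
- 134 evaluable: 0.99^134 = 26.0%.
- 191 per arm with missing counted as relapse (rates 0.7 × 1% = 0.7% and 0.7 × 8% = 5.6%): 0.993^191 = 26.1%.
- 191 per arm with no attrition: 0.99^191 = 14.7%.

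**4. What the model returns then.** For 0/134 versus 11/134, ordinary logistic regression stops at a log odds ratio of about 22 with a standard error of about 11,318, Wald p = 0.998. From the same fit the likelihood-ratio p is 0.00007. Fisher's exact p is 0.0008.

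**5. Exact power and type I error by test.** All pairs of independent binomial counts were enumerated at 134 per arm. Power counts rejections in favour of the intervention. Type I error counts both directions, at common null rates of 1%, 2%, 3% and 4.5%.

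| Test of the group effect | Power, 1% vs 8% | Type I error at 1 / 2 / 3 / 4.5% |
|---|---|---|
| Wald (separation = no rejection) | 54.6% | 0.0 / 0.3 / 1.4 / 3.2% |
| Score (pooled chi-square) | 84.2% | 2.4 / 4.5 / 4.4 / 4.7% |
| Firth penalised likelihood ratio | 84.0% | 0.6 / 2.5 / 3.7 / 4.6% |
| Ordinary likelihood ratio | 88.2% | 8.1 / 9.0 / 7.4 / 6.2% |
| Fisher exact | 75.1% | 0.1 / 0.9 / 1.7 / 2.2% |
| Wald with 0.5 added to each cell | 73.5% | 0.0 / 0.3 / 1.2 / 2.5% |

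The Wald test can never reject with no control events, and with one control event it needs at least 8 intervention events. The likelihood-ratio test rejects an empty control arm from 3 intervention events and the score test from 4. Wald power is 78.2% even with 191 per arm fully observed, and 51.0% under missing-as-relapse.

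**6. Check with a random intercept.** Simulation (400 replicates, 134 per arm in a mix of single persons and clusters of 7 to 11), maximum likelihood:
- No cluster variance: Wald 53.5%, likelihood ratio 86%.
- Assumed cluster SD of 0.6 on the logit scale: Wald 46%, likelihood ratio 84%, empty control arm in 33%.

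The cluster SD is an assumption, since the article gives no intracluster correlation (ICC). Type I error was not checked in this simulation.

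**The case against.** The strongest reply is that the article never commits to a Wald test. A logistic model also yields score, likelihood-ratio and penalised tests, and two of these keep both the stated power and the stated alpha under independence. In an empty-control trial the hypothesis test need not fail: the likelihood-ratio test rejects in 0.2598 of the 0.2601 probability of such trials. Sizing by two proportions and analysing by logistic regression is common and not itself an error. The choice of test is often left to a statistical analysis plan, which is not shown.

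Most of this stands. A reader might infer that logistic mixed regression fails in one trial in four, or that the planned analysis does not have 80% power. The documents do not support either statement without the added assumption of Wald inference.

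Two things remain. First, the missing finite odds ratio and Wald interval do not depend on which test supplies the p-value; they follow from the article's own rates and its own model under ordinary maximum likelihood. Second, the alternatives are not interchangeable: the ordinary likelihood-ratio test exceeds 5% type I error, the Fisher test and the 0.5-adjusted Wald test fall below 80% power, and the plain score test ignores the clusters that the article undertakes to model.

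**Conclusion.** The point holds in a conditional form. At the plan's design rates, 26% of trials would have no control abstainers, both at 134 evaluable per arm and at 191 per arm with missing counted as relapse. In those trials ordinary maximum-likelihood logistic (mixed) regression gives no finite odds ratio or usable Wald interval.

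Power of about 55% applies only if inference is by Wald test, which is assumed and not stated. Score and Firth penalised likelihood-ratio tests have 84% power with type I error below 5% at null rates of 1–4.5%. The ordinary likelihood-ratio test has 88% but type I error of 6–9%. These exact figures assume independent participants. The 80% claim is therefore neither confirmed nor refuted by the article; it depends on a choice between methods whose power runs from about 55% to 88%.

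**What to change.** For the primary binary outcome, replace ordinary maximum-likelihood/Wald inference with a named sparse-data method that also respects the residential clusters. Two options:

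- A Firth-type penalised logistic estimate, with a penalised likelihood-ratio test and interval and an allowance for clustering.
- A randomisation-based test on the risk difference, permuting individuals within their strata and residential programs within the short- and long-term strata, with a Firth-type odds ratio as the estimate.

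Which of these is chosen is a matter of preference. With either, report the risk difference with a cluster-respecting interval, and restate the power for the chosen method under a stated ICC.

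The cost is analysis wording and some programming. The restated power may be slightly lower: for the re-randomisation test, simulation with 267 completers (382 × 0.7; 1,000 replicates) gave about 77%, 74% and 73% at assumed ICCs of 0, 0.02 and 0.05. The 84% for the Firth test is an independence figure and would need the same recalculation with clustering.

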#### Rationale for Study Design

Due to the nature of the intervention under investigation (i.e., linking smokers to existing smoking cessation care options readily available in the community, quitline, and NRT) there is a high risk of contamination among residential services where participants are living under the same roof and hence may compare treatment received. Therefore, we will use a partial clustering design where cluster randomization will be used in situations where risk of contamination is particularly high (e.g., in residential services). Individual randomization will be used in settings where participants are approached individually (e.g., clinics). Conceptually, this can be considered as a cluster RCT where some clusters only contribute a single person (see statistical methods section). This is sometimes called a split-plot design (33).

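### The 80% power figure makes no allowance for clustering, although 210 of the 360 participants described are randomised in clusters of 10 to 15

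*Protocol article*

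**What the plan says.** Sample Size Determination assumes that "prolonged abstinence will occur in 1% of the control arm vs. 8% in the intervention arm". It continues: "To detect this effect with 80% power" "at *p* = 0.05, we require 134 per arm". The only later adjustment is for loss to follow-up: "We expect ~30% attrition, inflating the sample size to 191/arm or 382 overall". The paragraph mentions no ICC, cluster size or design effect.

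The rest of the protocol describes a partly clustered trial. Rationale for Study Design says: "Conceptually, this can be considered as a cluster RCT where some clusters only contribute a single person". Under Randomization, "cluster randomization will be used in situations where risk of contamination is higher, such as residential services", while other settings randomise individuals. The Statistical Methods section (Primary and Secondary Outcomes) gives the expected mix: 150 individually randomised people; 10 short-term programs, of which it says "the short-term residential programs are clusters that contribute an average of 15 people each"; and 6 long-term programs of 10. Cluster enters the planned mixed model as a random effect.

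**The concern.** People who share a residential program and an allocation tend to have more similar outcomes than people drawn independently, so each adds less information about the treatment effect. A power calculation that ignores this overstates what the trial can detect. Here more than half of the participants described are in randomised clusters, and the protocol itself presents the design as a cluster trial.

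The 80% is the benchmark against which a null primary result would be read. The introduction justifies the trial partly by the lack of an adequately powered trial of this kind, so an overstated figure would make a null result look more conclusive than the design allows.

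**Working it through.** **Inputs from the protocol.** Control rate 1%, intervention rate 8%, power 80%, significance level 0.05, 30% attrition, 191 per arm (all Sample Size Determination); 1:1 allocation (Randomization); 150 singletons, 10 clusters of 15, 6 clusters of 10 (Statistical Methods).

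**Assumptions.** A two-sided test, since sidedness is not stated. ICC 0.01 to 0.10, since none is given. The mix described for 360 people is applied to all 382 recruits.

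**1. Reproduce the plan's figure.** Two proportions, unpooled variance, individual randomisation:

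n = (1.96 + 0.8416)² × (0.01 × 0.99 + 0.08 × 0.92) / 0.07² = 133.75, so 134 per arm.

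134 / 0.70 = 191.4, stated as 191, and 2 × 191 = 382.

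Both steps agree with the plan, so no clustering allowance is hidden in either.

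**2. Share of participants in clusters.** 10 × 15 + 6 × 10 = 210, and 210 / 360 = 58%. The shares are 150/360 = 0.417 short-term, 60/360 = 0.167 long-term and 150/360 = 0.417 singletons.

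**3. Design effect.** With 30% attrition the clusters hold 15 × 0.7 = 10.5 and 10 × 0.7 = 7 completers:

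DE = 0.417 × (1 + 9.5 × ICC) + 0.167 × (1 + 6 × ICC) + 0.417 = 1 + 4.96 × ICC.

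**4. Power.** The variance is multiplied by DE: power = Φ(0.07 / √[0.0835 × DE / 134] − 1.96), where 0.0835 = 0.01 × 0.99 + 0.08 × 0.92.

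| Assumed ICC | DE | Effective n per arm (134/DE) | Power | Power, clusters weighted by precision |
|---|---|---|---|---|
| 0 | 1.00 | 134 | 80% | 80% |
| 0.01 | 1.05 | 127.7 | 78% | 78% |
| 0.02 | 1.10 | 121.9 | 76% | 77% |
| 0.05 | 1.25 | 107.4 | 71% | 72% |
| 0.10 | 1.50 | 89.6 | 63% | 67% |

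The last column replaces DE by 1 / Σ(share / DE of that stratum), which is closer to how a mixed model weights clusters.

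**5. Detectable difference.** Holding power at 80% and the control rate at 1%, the detectable intervention rate rises from 8% to about 8.5% at ICC 0.02 and 9.3% at ICC 0.05.

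**6. Sensitivity.**
- With full cluster sizes (15 and 10), DE = 1 + 7.33 × ICC and power is about 77%, 75%, 67% and 57% at the same four ICC values.
- Treating all 22 undescribed recruits (382 − 360) as singletons changes power by at most about 1 point.
- The pooled-variance formula starts from 79% rather than 80% at ICC 0 and runs about a point lower throughout.
- Unequal cluster sizes and the small number of residential clusters (16, about 8 per arm) would lower power further and are not counted.

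**The case against.** The strongest reply is that the shortfall depends on an ICC nobody has stated, and may be small. At ICC 0.01 the loss is 2 points. The upper range is also hard to support for so rare an outcome. With a 1% control rate, ICC 0.05 implies a between-cluster standard deviation of √(0.05 × 0.01 × 0.99) = 2.2 percentage points, and ICC 0.10 implies 3.1, two to three times the mean itself. The protocol clusters because of contamination, and counselling is delivered individually by telephone. This stands as a caution about size: the low end is the more plausible for the control arm, and 0.10 is best read as an outer bound.

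A second reply is that with 134 × 0.01 = 1.3 expected control events the normal approximation is rough. Exact calculation at 134 per arm without clustering gives 84% for an uncorrected chi-square test and 75% for Fisher's test. At the effective size for ICC 0.02 (122 per arm) the chi-square still gives 80%. So the choice of test moves power about as much as an ICC of 0.05 does. This also stands, and it means the table shows the loss relative to the plan's own formula, not an exact replacement value. It does not rescue the 80%: that figure comes from the approximation, and clustering lowers power whichever test is used.

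Third, the cluster mix is provisional, because the sites were not yet known, and the mixed model handles clustering, so the omission in the sample size does not bias the estimate or inflate type I error. Both are true, but neither makes 134 per arm include a design effect. Nor is the attrition allowance spare capacity, since the plan expects to use it.

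**Conclusion.** The concern holds. The stated 80% is the power of an individually randomised trial, and the protocol describes a different one. Under the plan's own formula, any positive ICC beyond the trivial rounding from 133.75 to 134 takes power below 80%.

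The direction is firm; the size is conditional. For ICC 0.01 to 0.05, power is about 78% to 71% with clusters reduced by attrition, and 77% to 67% at full cluster sizes. These figures rest on the assumed ICC, a two-sided test, the normal approximation and the 360-person mix carried over to 382. An ICC of zero is hard to defend as a silent assumption when the protocol expects people living together to compare their treatment and records living with other smokers as an influence on smoking.

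The arithmetic in the paragraph is correct as far as it goes. The error is that it was applied to the wrong design. The primary analysis remains valid.

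**What to change.** Rewrite the sample size paragraph to:

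- state an assumed ICC range, with the reason for it given the very low control rate;
- state the planned mix of singletons, 10 short-term and 6 long-term clusters, and say how the 382 recruits divide among them;
- report the power, or the detectable difference, that 382 recruits give under that mix: on the formula used here about 71% to 78% for ICC 0.05 to 0.01, or a detectable intervention rate of about 9.3% at ICC 0.05 and 8.5% at ICC 0.02;
- delete the unqualified 80%.

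Because so few control events are expected, the final figures should come from a small simulation using the planned mixed model, not from the normal approximation alone.

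The cost is one reworded paragraph and a short simulation. Enrolment, randomisation, endpoint and analysis model stay as they are. The price is a less favourable stated power.
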